#### Verum-2 stimulation.

The intensity will be adjusted according to the instructions provided to produce a mild, non-painful tingling sensation in the ear. The patients will be able modify the stimulation intensity during the study to ensure that it remains above this threshold.

#### Sham stimulation.

The intensity will initially be set to produce a mild tingling sensation in the ear that should not be painful. Subsequently, the intensity will be reduced to a level at which the patient no longer feels any stimulation. The stimulator will be maintained at this level throughout the study. However, participants in the sham group will receive an ear electrode provided by the manufacturer, which is based on a regular electrode but does not establish an electrical connection between the stimulator and ear contact, ensuring no actual stimulation occurs.

### Study procedure

The study commenced on 1^st^ September 2023. As there is no central point of contact for patients with long covid, all participants were/will be informed about the study by their general practitioners. Contact will be established between general practitioner networks and local support groups. General practitioners can identify suitable patients based on the inclusion and exclusion criteria, and referred them to the study investigator. The two visits (“Visit 0” and “Visit 1”) and the telephone interview will subsequently be scheduled following consultation with the patient.

During the study period, participants will use the “tVNS Patient” app developed by tVNS Technologies GmbH (available for free in the respective app stores) to automatically document the frequency and duration of stimulations. Compliance documentation will be provided, as recommended in the 2020 consensus paper on noninvasive VNS [21]. Only the patient can access these data, which will be finally reviewed by a physician at the end of the stimulation period. All data will be stored exclusively on participants’ smartphones. The questionnaires will be entered and analyzed as electronic case report forms (eCRFs) in the RedCap system of the Department of Medical Informatics.

#### Visit 0.

During the initial visit, patients will receive informational documents, sign informed consent forms, and complete the questionnaires. Personal data such as age, sex, height, weight, therapy time, duration, and type will also be documented. The patients will receive the stimulator and be instructed regarding its use by the investigator, according to the guidelines of the German Medical Devices Act (MPG/MPDG). Additionally, group assignment (SHAM, Verum 1, or Verum 2) will be performed. Subsequently, the 4-week stimulation phase will be initiated.

#### Telephone interview after 7 days.

After 7 days, patients will be contacted by phone or email (if preferred) to inquire about their use of the stimulator, any side effects, or any potential questions they may have.

##### Visit 1

After 4 weeks, the patients will complete the questionnaires again. Personal data, including weight, will be collected, while data regarding the duration of stimulation will be retrieved from a smartphone. Subsequently, the stimulators will be returned. Patients who cannot attend visit 1 because of their health conditions will receive online access to the questionnaire section of the eCRF to complete it from home.

#### Optional Visit 2 (optional cross-over-design).

Patients enrolled in “Sham” or “Verum 1” will be offered to receive “Verum 2” stimulation for 4 weeks at the end of the study.

**The study will be terminated here.**

## Discussion

### Safety

Several studies have shown that healthy patients undergo acute taVNS to investigate scientific questions in behavioral research [57–59]. Although mild side effects may occur, none of the existing studies on this topic have reported any severe side effects. TaVNS was also investigated in a medical doctoral thesis involving healthy patients without relevant side effects [60]. In total, the cited studies included >1,200 healthy patients who underwent taVNS without any difficulty. Although the occurrence of side effects correlates with the duration of stimulation [61], even during chronic taVNS, which lasts several weeks, only a few adverse effects and no severe events have been observed [13,56,62].

A recent review of transcutaneous VNS (including both cervical and auricular stimulations) reported skin redness (16.7%), headache (3.3%), nasopharyngitis (1.6%), and nausea/dizziness (1.1%) as the most common side effects among 1,322 patients. Only 2.6% of all patients had to discontinue the study because of side effects, while facial palsy occurred only with cervical vagus nerve stimulation [55]. Long covid and its associated fatigue syndrome pose a challenging burden for both patients and healthcare systems. Investigating a noninvasive method to improve this devastating condition may be extremely beneficial, and this goal could justify these known side effects. The results of this pilot study will be analyzed with respect to subsequently conducting a full multicenter interventional study, and will provide information regarding future inclusion and exclusion criteria, recruitment rate, sample size, expected adherence, and dropout rates among patients with long covid-associated fatigue.

### Ethics and regulatory aspects

This study was approved by the local ethics committee of Ruhr-University-Bochum under registration number 23/7798 on 05/12/23, with amendment acceptance on 06/14/23. It was further registered in the DRKS-System under the number DRKS00031974 (https://drks.de/search/de/trial/DRKS00031974) on 05/25/23. The accepted version was version 3.0, from 06/14/23, and the sponsor was the University Medical Center Knappschaftskrankenhaus Bochum. The study will be performed under the §47(3) of the new MPDG law defining clinical studies involving medical devices. As the tVNS-L-System, owing to the fixed set of stimulation parameters, possesses a CE mark for vagal nerve stimulation, and this study involves no invasive procedures, ethical approval was relatively simple and rapid to obtain. Thus, if the results indicate feasibility, a larger study could be quickly initiated with a CE-certified system, in contrast to a system that does not have a CE mark.

### Sham intervention

Defining the sham group in a stimulation study is challenging. Several different approaches have been discussed in the literature, including stimulation of the ear lobe instead of the cymba conchae, or stimulation of other parts of the body [63–66]. However, an informed patient may realize that such stimulation is different from normal taVNS, and could thus identify themselves as being in the sham group. To address this, patients will alternately provide with information that they will either feel or do not feel the stimulation. Once the tingling sensation has been demonstrated to the patient, the intensity will be reduced until the patient does not feel any stimulus. The sham group will then be provided with a non-functional electrode, while the verum-1-group will maintain their functional electrode throughout the study phase. If the analysis shows that both the verum-1 and verum-2 interventions have a significant effect on fatigue, future studies will need only one subthreshold group and one sham group, leaving the patients blinded to which group they have been included in.

Within this feasibility trial, no invasive procedures, such as blood sampling, has been planned, in order to maintain the regulatory requirements as low as possible. The stimulation system tVNS-L® is manufactured by tVNS GmbH in Erlangen, Germany. This system allows modification of the stimulation intensity but not of the pulse width or frequency. As such, it is a CE-mark for transcutaneous auricular vagal nerve stimulation. The variant tVNS-R® (R for research) allows modification of all parameters; consequently, it does not have a CE-mark, making it extremely difficult to obtain insurance and ethical approval for a scientific study.

The results of this study will be published in scientific, probably open-access, journals with a scope for public health. If taVNS, as a very safe procedure, can improve fatigue and the challenging sequelae of long covid, it would significantly improve the quality of life of such patients. This potential improvement in the quality of life justifies the extremely low risk of taVNS therapy in this study.

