### Selection of patients and data collection

A total of 45 patients will be recruited and divided into three groups. Patients will be informed about the study through flyers and by their general practitioners, and will be provided with access to a website. Additionally, local support groups will be contacted and informed. On the website, questions regarding the inclusion and exclusion criteria will be asked anonymously, without data storage. At the end of the questionnaire, patients will be informed of whether they qualified for the study. In the case of study qualifications, patients will be provided with an email address where they can sign up to participate. Patients will be informed about the study aims and procedures by an investigator or certified medical professional. After obtaining written informed consent, data collection will be pseudonymized in the RedCap electronic case report form (eCRF) system of Ruhr-University-Bochum and will be General Data Protection Regulation (GDPR)-compliant. The RedCap system automatically randomizes patients into Verum-1, Verum-2, or Sham groups (n = 15 each). The patients will be instructed on how to use the simulator for 4 h per day, with at least 1 h of consecutive stimulation in the left ear. Patients will be asked to log all stimulation times manually in a diary. Because patients in the sham group will also receive the device’s user manual, which states that they should feel a tingling sensation in the ear, they will be instructed to use the highest stimulation intensity that is not perceptible to them. After adjusting the stimulation to this level, sham patients will receive a non-functional electrode that does not perform any stimulation. This approach is justified as the principle “more is better” does not apply to vagus nerve stimulation, and stimulation below the perception threshold could still, theoretically, have an effect.

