#### Verum-1 stimulation.

The intensity will initially be set to produce a mild tingling sensation in the ear that should not be painful. Subsequently, the intensity will be reduced to a level at which the patient no longer feels the stimulation. The patient will then be asked to repeat this procedure every time stimulation is initiated to ensure that the stimulation is always subthreshold.

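### Sham patients change electrode after the tingling demonstration and Verum-1 patients do not, so the hand-over differs by arm and could reveal allocation

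*Protocol article*

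**What the plan says.** The protocol article describes the start of stimulation in the two subthreshold arms in several places.

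- **Discussion, Sham intervention.** The demonstration comes first: "Once the tingling sensation has been demonstrated to the patient, the intensity will be reduced until the patient does not feel any stimulus". The arms then part: "The sham group will then be provided with a non-functional electrode, while the verum-1-group will maintain their functional electrode throughout the study phase".
- **Selection of patients and data collection.** The order for sham is the same: "After adjusting the stimulation to this level, sham patients will receive a non-functional electrode that does not perform any stimulation".
- **Sham stimulation.** The sham patient feels mild tingling before the intensity is lowered. On the study electrode, the text says that "participants in the sham group will receive an ear electrode provided by the manufacturer, which is based on a regular electrode", but that it makes no electrical connection between stimulator and ear.
- **Verum-1 stimulation.** The patient goes through the same tingling-then-reduce sequence. No change of electrode is described.
- **Visit 0.** The stimulator is handed over and explained at this visit, and "Additionally, group assignment (SHAM, Verum 1, or Verum 2) will be performed".

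The Sham intervention section also gives the reason for this design. Other kinds of sham are set aside because an informed patient "could thus identify themselves as being in the sham group".

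**The concern.** The sham was chosen so that patients would not recognise it. Verum-2 patients are meant to feel tingling throughout, so sensation separates them from the other two arms. Sham versus Verum-1 is the only contrast in which neither arm is meant to feel stimulation after set-up, and so the only one where the patient might stay unaware of the arm. The exchange falls within that contrast.

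The MFI20, BDI, SF36 and PCS-Score are patient questionnaires, and the primary outcome, daily stimulation time, is patient behaviour. Both can respond to what a patient believes about allocation. The contrast also bears on the next trial: the article says that, if subthreshold stimulation works, future studies could use one subthreshold arm and one sham arm with patients blinded. A cue in the hand-over procedure would carry over into that trial if the procedure were copied.

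**Working it through.** No formula applies, and no figure in the plan changes. The check sets the sections side by side.

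1. **Demonstration.** Sham: tingling is felt, then reduced until not felt (Sham stimulation; Sham intervention). Verum-1: the same (Verum-1 stimulation; Sham intervention). No difference so far.
2. **Electrode used for the demonstration.** Tingling requires an electrode that conducts. The sham study electrode does not. The sham patient therefore starts on one electrode and continues on another.
3. **Electrode used afterwards.** Sham: a non-functional one, supplied after the level has been set (stated in both Selection of patients and data collection and Sham intervention). Verum-1: the functional one is kept (Sham intervention).
4. **Timing.** Hand-over, instruction and group assignment are all placed at Visit 0, after which the 4-week stimulation phase starts. The article describes no other in-person visit before stimulation, so the exchange is most naturally read as taking place at Visit 0. That section itself does not mention electrodes.
5. **Count.** With 15 patients per arm, the exchange as written occurs in 15 of 15 sham patients and 0 of 15 Verum-1 patients. This shows that the procedure is arm-specific. It does not measure how many patients would be unmasked.
6. **What is not stated.** The article does not say whether the exchange happens in the patient's view, what the patient is told about it, or whether patients know that an exchange goes with sham.
7. **Home use.** A second difference lies outside the hand-over. For Verum-1, "The patient will then be asked to repeat this procedure every time stimulation is initiated". For sham, "The stimulator will be maintained at this level throughout the study". A Verum-1 patient who follows the instruction feels tingling again at each session. A sham patient who raised the intensity would feel nothing. Making the hand-over identical would leave this difference in place.

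**The case against.** The strongest reply is that a difference in procedure is not a demonstrated unmasking. A reader might infer that the hand-over itself tells patients which subthreshold arm they are in. The document does not support that. It says only that sham patients receive, or are provided with, the electrode. Each patient sees only their own set-up and has no comparator, and the sham electrode is derived from a regular one, which is the plan's own concealment measure. A reader might also infer that participants recruited through support groups would compare their visits, or that sham patients would use the device less and report less improvement. Nothing in the document establishes either. The effect sought for subthreshold stimulation is 5 MFI units (Sample size calculation), but no figure for an expectation effect is given to set against it.

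It can also be argued that the sentence about Verum-1 keeping its electrode only describes which type each arm uses over the 4 weeks, and that visibility, coding and staff wording belong in the full protocol, which is not shown. On visibility and coding this stands, and their absence is not held against the plan. It does not remove the point. Two sections give the sequence for sham in affirmative words, and the prior tingling makes a change of electrode unavoidable there. A look-alike electrode hides what the new object is, not that an exchange took place.

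Lastly, this is a feasibility pilot, and the article speaks of blinding patients only for future studies. That lowers the stakes, but the stated aim of preventing sham recognition applies to this trial.

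**Conclusion.** The point holds in a limited form. As written, the electrode is changed after the demonstration in sham and kept in Verum-1. The hand-over therefore differs by arm and could reveal allocation in the sham versus Verum-1 contrast, which works against the plan's own reason for choosing this sham.

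The asymmetry rests on the text and on one inference, that a patient who has felt tingling must have worn a conducting electrode. Placing it at Visit 0 rests on hand-over and assignment both being listed there. Whether patients notice or interpret the exchange is unknown, and the size and direction of any bias cannot be determined from the document. The change is still worth making, because it removes a cue from the one contrast that could be masked and costs little.

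**What to change.** Make the hand-over identical in all three arms. One way is to run the threshold demonstration on a separate electrode in every arm, then give every patient a coded, identically packaged take-home electrode, functional or non-functional by allocation, with the same words said at the exchange. Amend Selection of patients and data collection, Sham stimulation and Sham intervention to say so.

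Reconcile the home-use instructions in Verum-1 stimulation (procedure repeated at each session) and Sham stimulation (level kept fixed). Without this, an identical hand-over does not secure masking.

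The study started on 1 September 2023, so the change can apply only to patients not yet enrolled and to the follow-on trial. For patients already enrolled, report the arm-specific exchange as a limitation.

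**Cost.** If every verum patient needs one additional electrode, that is 45 − 15 = 30, plus protocol wording. A reusable demonstration electrode would need fewer. The document gives neither electrode prices nor reuse rules, so both figures are assumptions. No extra visit is needed.

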### Data protection, management, and monitoring

Only pseudonymized data will be stored on the RedCap®-System in our hospital, while a table containing patient records will be stored on a different drive within the hospital network. Only the investigator and study nurses will have access to the database, and the rules of the GDPR will be applied. Data monitoring will be performed by the Department of Medical Informatics, Biometry, and Epidemiology at Ruhr-University Bochum, which runs and maintains the RedCap system. The results of the study will be made available in peer reviewed journals.
